### Trial design

This study is a prospective, randomized, controlled, multicenter, superiority study comparing the laparoscopic and open approaches for emergency colorectal resections. The primary endpoint is postoperative morbidity. The trial is independent of any kind of commercial sponsorship. The flow chart of the study is presented in the (Fig. 1).

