### Outcomes

The main endpoint of the study will be 30-day postoperative morbidity, which will be evaluated from the Comprehensive Complication Index (CCI) of all patients. CCI is the sum of all complications weighted on with their severity based on the Clavien-Dindo classification (CCI = √(*wC* + *wC*2 + … + *wCx*)/2) and has values ranging from 0 to 100 [24].

The secondary endpoints of the study are as follows.

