### Statistical methods

The findings will be analyzed using SPSS (version 27 or higher) (IBM Corp., Armonk, NY, USA) for Windows. Both intention-to-treat and per-protocol analyses will be performed.

Between-group comparisons of continuous variables will be performed using Student’s *t* test or with the Mann–Whitney *U* test if heterogeneous variances persist. Categorical data will be compared using the *χ*^2^ test or Fisher’s exact test. Long-term survival will be analyzed using Cox regression or Kaplan–Meier’s analysis. Two-tailed *p* values will be reported. *P*-values ≤ 0.05 are considered significant. If data for a certain variable is missing the case will be removed from the analysis in question.

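### The test for the primary CCI endpoint depends on the observed variances, with Mann–Whitney as the response to unequal variances; one analysis should be fixed in advance

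*Protocol article*

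**What the plan says.** Outcomes defines the primary endpoint through a numeric score: "The main endpoint of the study will be 30-day postoperative morbidity, which will be evaluated from the Comprehensive Complication Index (CCI) of all patients". The score weights complications by severity and "has values ranging from 0 to 100".

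Statistical methods has one sentence for all numeric outcomes. It opens "Between-group comparisons of continuous variables will be performed using" Student's t test, and moves to the Mann–Whitney U "test if heterogeneous variances persist". The CCI has no rule of its own. No check of heterogeneity, threshold or effect measure is named. Tests are two-sided with significance at 0.05.

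The Sample size section plans on two proportions, 48.3% morbidity after open surgery and 27.8% after laparoscopy, so it does not settle how the CCI is to be tested.

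**The concern.** Two things are wrong with the rule as stated.

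- **The remedy does not fit the trigger.** If the aim is to compare means under unequal variances, the remedy is a Welch test or robust standard errors. Mann–Whitney asks whether a patient in one arm tends to score higher than a patient in the other, which is not a difference in mean burden.
- **The data choose the question.** The CCI is likely to be zero for many patients. With many zeros, ranks mostly reflect whether a patient had any complication, while the mean carries the severity weighting for which a CCI is used. A real difference in complication rates also changes the variances, so the treatment effect itself can set off the switch.

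The Discussion section says that laparoscopy may carry risks not yet recognised, so a pattern of fewer but worse complications cannot be ruled out. In that pattern the two tests can disagree. The check that decides between them is unnamed and could be settled after the data are seen.

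**Working it through.** **Inputs from the protocol.** Complication rates 48.3% (open) and 27.8% (laparoscopic), 87 evaluable patients per arm, 80% power (Sample size); CCI from 0 to 100 (Outcomes); two-sided 0.05 (Statistical methods).

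**Assumptions, not in the protocol.** CCI is zero without a complication, and the morbidity rates equal the share with CCI above zero. Severity among patients with a complication is gamma with mean 25 and CV 0.6, capped at 100. As a second model it is a scaled beta on 0–100 with mean 25 and CV 0.5. The variance check is Levene's test at 0.05, mean-centred or median-centred.

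**1. The plan's own figure.** n = [1.960·√(2·0.3805·0.6195) + 0.8416·√(0.483·0.517 + 0.278·0.722)]² / 0.205² = (1.346 + 0.565)² / 0.0420 = 86.9, so 87 per arm. The stated figure reproduces (power 80.1%), as a test of two proportions.

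**2. Share of zeros.** 1 − 0.483 = 51.7% (open); 1 − 0.278 = 72.2% (laparoscopic).

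**3. What each test compares, equal severity.**
- Mean difference: (0.483 − 0.278) × 25 = 5.1 CCI points.
- Mann–Whitney: the probability that an open patient scores higher than a laparoscopic one, ties counted half, is 0.483·0.722 + ½·0.483·0.278 + ½·0.517·0.722 = 0.349 + 0.067 + 0.187 = 0.6025. This equals ½ + ½(0.483 − 0.278), so it depends only on the rates of any complication.
- Had every laparoscopic complication scored above every open one, the middle term would vanish and the value would still be 0.535, above ½. At these rates severity cannot reverse the rank comparison.

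**4. Why the planned effect triggers the switch.** For the gamma model, ignoring the cap, variance = p·m²(1 + CV²) − (p·m)².
- Open: 0.483·850 − 12.075² = 264.7.
- Laparoscopic: 0.278·850 − 6.95² = 188.0. The ratio is 1.41.
- Power of a mean comparison: 5.125/√226.4 = 0.341; 0.341·√(87/2) = 2.25; Φ(2.25 − 1.96) ≈ 61%. The gamma simulation gives 61.0%.

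**5. Equal-mean case.** Equal mean CCI at the planned rates needs laparoscopic complications 0.483/0.278 = 1.74 times as severe (mean about 43 against 25).

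**6. Simulation, beta model, 87 per arm, 5,000 trials per row.** Paired entries are mean-centred / median-centred Levene.

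| Scenario (open / laparoscopic rate) | Switch to Mann–Whitney | t rejects | Mann–Whitney rejects | Rule rejects |
|---|---|---|---|---|
| Identical arms, 48.3% | 12.0% / 5.2% | 4.6% | 4.7% | 3.6% / 3.8% |
| Planned, 48.3 / 27.8, same severity | 61.0% / 67.1% | 66.3% | 77.2% | 67.0% / 66.5% |
| Equal means, 48.3 / 27.8 | 65.0% / 5.2% | 5.3% | 44.8% | 19.0% / 3.7% |
| Equal means, 60 / 40 | 85.2% / 9.7% | 5.1% | 24.2% | 16.7% / 3.1% |
| Equal means, 48.3 / 38 | 40.5% / 5.9% | 5.5% | 11.6% | 3.8% / 4.0% |
| Equal means, 48.3 / 43 | 22.3% / 5.9% | 5.1% | 6.6% | 3.5% / 3.8% |

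In the 48.3 / 27.8 equal-means row, an open-arm severity mean of 20 or 30 instead of 25 gives 16.9% or 19.7% for the rule with the mean-centred check.

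**7. Gamma model** (3,000 to 6,000 trials per run where recorded).
- Planned effect: the switch fires in about 56% to 63% of trials over both checks. Power is 61.0% (t), 76.3% (Mann–Whitney) and 61.6% (rule).
- Equal means at the planned rates: t 4.9%, Mann–Whitney 47.3%, rule about 14% to 17% mean-centred and 3.1% to 3.8% median-centred.
- Identical arms: rule 3.3% to 3.7%.

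**8. Two further readings.** The t test and Mann–Whitney reach different verdicts in 12% (beta) to 17% (gamma) of trials under the planned effect, and in about 43% to 44% in the equal-means case at the planned rates. With equal arms, Student's t and Welch hardly differ (5.3% each at equal means, 66.3% each under the planned effect), so in this design the switch guards against very little.

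**The case against.** The case for leaving the rule alone has several sound parts.

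- **Type I error is not inflated.** With identical arms the rule rejects in about 3% to 4% of trials, which is conservative. A reader might infer that the smaller of two p-values could be picked; the protocol describes no such procedure.
- **The rule is not built to favour laparoscopy.** A reader might infer a bias in that direction from the 14% to 19%. That figure needs a rate gap of about 20 points, an offsetting severity ratio of about 1.7 that nothing in the protocol gives, and a mean-centred check. With a median-centred check, or a gap of about 10 points or less, there is no excess. The mirror pattern would favour open surgery.
- **Mann–Whitney is not wrong on its own terms.** When complication rates differ, the distributions differ, and rejecting their equality is correct. The protocol does not name a mean difference as its target.
- **The zeros are an assumption.** The rates come from an earlier study, and the protocol does not show that its morbidity definition equals a CCI above zero.
- **The sentence is generic and the article condensed.** A separate analysis plan may name the CCI test, and the word persist may hint at a prior transformation, although none is described.

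These points limit the size and direction of the harm. They do not rescue the rule. It is stated, it covers the CCI, it lets the variances choose the question, and it answers unequal variances with a test that does not address them. An analysis plan that followed it would inherit the fault.

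**Conclusion.** The point holds as a should-fix. That the test depends on the observed variances, and that Mann–Whitney is the stated response to unequal variances, follows from the text and needs no simulation.

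The sizes rest on the assumed share of zeros, the assumed severity distribution and a Levene check. Under the planned effect and the gamma model, which question gets answered is close to a coin toss with either form of the check, although the verdict itself would differ in only 12% to 17% of trials across the two severity models. In the fewer-but-worse pattern the chance of a significant result at equal mean CCI moves from about 3% to 4% up to about 14% to 19%, depending only on how an unnamed check is centred. The documents do not support a claim of general type I inflation or of a built-in advantage for laparoscopy.

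**What to change.** Delete the variance trigger and pre-specify one primary CCI analysis with its effect measure, used whatever the variances turn out to be. Either of these would serve:

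- difference in mean CCI with a 95% confidence interval from Welch or robust standard errors, which keeps the severity weighting; or
- Mann–Whitney with a rank-based effect measure.

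Report the other one, and the proportion with any complication, as named sensitivity analyses. Apply the same no-switching rule to the other continuous endpoints.

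The cost is one or two sentences, through the route in the Protocol amendments section; the Trial status section reports 75 of the planned 192 patients enrolled. The choice has a price in power. Under the gamma assumptions the mean-based test has about 61%, the same as the rule as written, but about 15 points less than a fixed Mann–Whitney test (about 76%) if laparoscopy changes only how often complications occur. Both are below the planned 80%. The investigators should choose according to whether total burden or the tendency to score lower is the question, and record the reason.

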## Background and rationale

The first laparoscopic colon resection for colorectal cancer was performed in 1990. In the beginning, there were concerns about achieving adequate oncological results with the laparoscopic technique. Additionally, there were considerable numbers of port site metastases in the 1990s which over time diminished along with the development of laparoscopic instrumentation [1]. Initial doubts were quite soon dispelled, and laparoscopy was proven to be both safe and equal to open surgery in terms of the oncological results [2–4]. Patient recovery was also faster, postoperative ileus occurred less often, and overall morbidity was lower [4–6]. As a result, laparoscopy proved to be cost-effective [7].

Today, laparoscopic colorectal resections are well established in elective surgery, although the role of laparoscopy in emergency operations remains uncertain [8, 9]. It may be expected that the same benefits achieved with minimally invasive techniques in elective surgery also advocate the use of laparoscopy in emergency operations [10–12]. There are, however, several concerns regarding laparoscopy in emergency settings. The operations are technically more challenging due to distortion of the normal anatomy and the presence of a dilated vulnerable bowel [13]. Intra-abdominal lavage in inflammatory processes might be less effective [14] and the operation takes longer, which could be a disadvantage for the critically ill patient [15].

Approximately 10–20% of colorectal resections are carried out as emergency operations, which are associated with a higher risk of in-hospital mortality, double the risk of reoperation, and a three times higher risk of failure to rescue, compared to elective surgery [16–18]. The type of complication varies greatly depending on whether the operation has been elective or emergency, which most likely also reflects the type of technical approach. For example, fascial rupture is almost three times more common after emergency surgery [18]. In many other entities demanding emergency surgery, the laparoscopic approach has proven to diminish both morbidity and mortality [19] and can therefore be assumed to do the same in colorectal surgery.

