### Objectives

The objective of this study is to evaluate whether patients benefit from the laparoscopic approach in emergency colorectal surgery, whether benign or malignant disease.

Our hypothesis is that the same beneficial effects of laparoscopy seen in elective surgery and in other entities needing emergency surgery will also apply to emergency colorectal surgery. These benefits are lower overall postoperative morbidity, shorter in-hospital stay, less postoperative ileus, less postoperative pain, fewer wound complications, and lower risk of mortality.

For oncologic patients, our hypothesis is that the laparoscopic approach is superior to the open approach, partly because of the faster recovery associated with greater access to oncologic treatment and partly because in laparoscopy the intra-operative circumstances need to be optimized to mimic the elective situation, leading to good visualization and a standardized approach.

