#### Overall survival (OS)

OS is defined as the time (years) from initial cancer treatment to death for any reason.

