#### Cancer-specific survival (CSS):

CSS is defined as the time (years) from initial cancer treatment to death caused by the same cancer.

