#### Disease-free survival (DFS)

DFS is defined as the time (years) from initial cancer treatment to recurrence of the cancer or death for any reason.

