### Participant timeline

Recruitment of patients started in September 2021 at Päijät-Häme Central Hospital and will last for 3–4 years. The estimated enrolment schedule is presented in Table 1. The progress of enrolment is expected to vary between participating hospitals because of differences in the annual caseloads of emergency colorectal diseases. The endpoint of the study is when the final patient recruited reaches the 90-day follow-up and for the oncologic assessment when the final patient recruited reaches the 5-year follow-up or dies.

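### For cancer-specific survival, one minus Kaplan-Meier overstates the 5-year probability of cancer death; report a cumulative incidence curve and keep the Cox hazard ratio, labelled as cause-specific

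*Protocol article*

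**What the plan says.** The Protocol article lists three long-term survival outcomes for oncologic patients.

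- CSS: "CSS is defined as the time (years) from initial cancer treatment to death caused by the same cancer".
- Overall survival (OS): "OS is defined as the time (years) from initial cancer treatment to death for any reason".
- Disease-free survival (DFS): "DFS is defined as the time (years) from initial cancer treatment to recurrence of the cancer or death for any reason".

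One sentence under Statistical methods covers all three: "Long-term survival will be analyzed using Cox regression or Kaplan–Meier’s analysis". The article names no competing-risk method. It does not say how a death from another cause is handled in CSS, or whether a death after the emergency resection of a cancer counts as a cancer death.

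The Participant timeline section ends oncologic follow-up "for the oncologic assessment when the final patient recruited reaches the 5-year follow-up or dies". Background and rationale describes emergency colorectal resections as operations "which are associated with a higher risk of in-hospital mortality" than elective ones, without a rate. The Objectives section lists "fewer wound complications, and lower risk of mortality" among the hypothesised benefits of laparoscopy, again without a rate and without a split by cause.

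**The concern.** OS and DFS count every death as an event, so no death competes with them. CSS is different. A patient who dies of sepsis, an anastomotic leak or a comorbidity can no longer die of the cancer, so that death is a competing event. Ordinary Kaplan-Meier knows only events and censored times. It must censor that patient, and it then treats them as someone who could still have had the event later. One minus the curve estimates the risk of cancer death in a hypothetical setting where nobody dies of anything else.

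A 5-year CSS curve is usually read as an absolute probability: how many of these patients died of their cancer. Read that way, the figure would be too high in both arms. After emergency surgery some competing deaths fall early, and these displace the most follow-up. The Discussion presents the oncologic outcome as a distinctive part of the trial, so the figure is likely to be quoted.

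**Working it through.** **The plan's own figures.** The article gives no event rate, number of patients or precision for CSS, so there is nothing to reproduce. The sample size of 87 per group concerns the primary endpoint and does not enter here.

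**Direction, without any assumed rate.** Let h(t) be the cancer-death hazard, H(t) its cumulative value, and S_o(t) the probability of not yet having died of another cause. Over 5 years:

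- one minus Kaplan-Meier estimates ∫ h(t)·exp(−H(t)) dt;
- the cumulative incidence of cancer death is ∫ h(t)·exp(−H(t))·S_o(t) dt.

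S_o(t) never exceeds 1 and falls below it once anyone dies of another cause. The first integral is therefore always the larger.

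**Size, under assumed rates.** None of these inputs is in the article:

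- net 5-year cancer death (the one-minus-Kaplan-Meier figure) 30-50%, central 40%, constant hazard;
- non-cancer death by 90 days 5-15%, central 10%, constant hazard within that period;
- non-cancer death afterwards 2-5% a year, central 3%.

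Central case, with 90 days = 0.246 years:

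- cancer hazard = −ln(0.60)/5 = 0.1022 per year;
- early non-cancer hazard = −ln(0.90)/0.246 = 0.428 per year; later hazard 0.03 per year;
- cancer deaths in the first 90 days = 0.1022/(0.1022+0.428) × (1 − exp(−0.530×0.246)) = 0.024;
- alive at 90 days = exp(−0.530×0.246) = 0.878;
- cancer deaths from 90 days to 5 years = 0.878 × 0.1022/0.1322 × (1 − exp(−0.1322×4.754)) = 0.316;
- cumulative incidence = 0.024 + 0.316 = 0.340.

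One minus Kaplan-Meier is 0.400, so the excess is 6.0 points.

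| Net cancer death | 90-day non-cancer death | Later, per year | 1 − KM | Cumulative incidence | Excess |
|---|---|---|---|---|---|
| 30% | 5% | 2% | 30.0% | 27.4% | 2.6 points |
| 40% | 10% | 3% | 40.0% | 34.0% | 6.0 points |
| 50% | 15% | 5% | 50.0% | 38.8% | about 11 points |

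For scale, suppose 50-70% of the 96 patients per arm have cancer, which gives 48 to 67 (also an assumption). The Greenwood standard error of the central Kaplan-Meier estimate is then 7.7 to 6.5 points, so the 6-point excess is 0.8 to 0.9 of a standard error.

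**A second, simpler model.** Put the early non-cancer deaths (fraction q) at time zero and use constant hazards λc (cancer) and λo (other) afterwards. Cumulative incidence = (1−q)·λc/(λc+λo)·(1−exp(−5(λc+λo))). With one minus Kaplan-Meier at 30%, net other-cause death at 10% and q of 3%, 5%, 10% and 15%, it is 27.7%, 27.1%, 25.7% and 24.3%. The excess is 2.3 to 5.7 points. Over a wider grid (cancer death 20-50%, other-cause death 5-20%, q 3-15%) it runs from 1.1 to 11.4 points, a ratio of 1.05 to 1.31.

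**Arm contrast.** Take equal cancer hazards (net 40%), later non-cancer death of 3% a year, and 90-day non-cancer death of 12% open against 5% laparoscopic. Kaplan-Meier shows 40.0% in both arms and the cause-specific hazard ratio is 1.00. The cumulative incidences are 33.3% open and 35.8% laparoscopic. That 2.5-point difference compares with a binomial standard error of √[(0.333×0.667 + 0.358×0.642)/n], which is 9.7 points at n = 48 and 8.2 at n = 67.

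**The case against.** The strongest reply has four parts.

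*The arm comparison is already valid.* A reader might infer that Cox regression is also wrong here and that the comparison of arms is biased. The document does not support that. A Cox model that censors other-cause deaths estimates the cause-specific hazard ratio, which is a standard target when the question is the oncologic adequacy of the operation. In the example above it correctly returns 1.00. A Gray or Fine-Gray comparison would lean towards the open arm only because more of its patients died early of other causes. Making either one the main contrast is a choice of estimand and corrects no error. This part stands in full.

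*CSS hides nothing.* A reader might also infer that excess postoperative deaths in one arm would disappear from view. They would not: OS, DFS and the separate 90-day mortality endpoint all count death from any cause. This stands.

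*The rates are not in the document.* The background section says only that in-hospital mortality is higher than in elective surgery. The hypothesised benefit is "fewer wound complications, and lower risk of mortality", which is mortality overall and not non-cancer death in cancer patients. This stands, so every size above is conditional on assumptions, and an arm difference in the competing event is a possibility with no stated size.

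*Censoring is inferred, and a condensed article leaves detail to a fuller plan.* This stands only in part. The article does not mention censoring, but the CSS definition and an ordinary Kaplan-Meier estimator leave no other status for such a death. The point also concerns a method the article does state, and not an omitted detail. How postoperative deaths are attributed is truly open. If they were counted as cancer deaths, the excess would shrink, but CSS would then absorb surgical mortality.

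**Conclusion.** The point holds for the Kaplan-Meier option applied to CSS. One minus Kaplan-Meier overstates the 5-year probability of cancer death in any trial with deaths from other causes, and that direction needs no assumed rate. The size does: about 6 points in the central case and about 2.6 to 11 points over the stated range, none of it derivable from the article. It also assumes that postoperative deaths are mostly not classed as cancer deaths.

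The Cox option is not at fault and may remain the main comparison of arms. The effect on any comparative conclusion is likely to be small: in the worked example, 2.5 points against a standard error of 8 to 10. The problem is confined to one secondary outcome in the oncologic subgroup. The primary endpoint, OS and DFS are unaffected. This is a cheap improvement.

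**What to change.** Amend the survival sentence under Statistical methods, or the analysis plan, so that for CSS:

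- the cumulative incidence of cancer death (Aalen-Johansen), with death from any other cause as a competing event, replaces one minus Kaplan-Meier;
- the cumulative incidence of non-cancer death is shown by arm beside it;
- the Cox hazard ratio is kept for the arm contrast and labelled as cause-specific, with Gray's test or a Fine-Gray model optional;
- the rule for classifying postoperative deaths as cancer or non-cancer is stated in advance and applied identically in both arms.

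Kaplan-Meier and Cox stay as they are for OS and DFS.

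The cost is a few lines of text and of code, possibly outside base SPSS. No new data are needed, because CSS already requires the cause of death. The price is a somewhat lower headline figure for cancer death and one more curve. The final CSS assessment waits for the last patient's 5-year follow-up, so there is time to fix this before the analysis.

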### Sample size

Sample size calculations will be based on previous studies, which report 48.3% 30-day postoperative morbidity after open surgery and 27.8% after laparoscopy [22]. The aim of the study is to show that postoperative morbidity is lower after laparoscopic surgery. Assuming *α* = 0.05 and a (?) power = 80, 87 patients are needed for both groups. The effect size is 0.54. Assuming a 10% patient drop-out rate during the 30-day follow-up period, a total of 192 patients, i.e., 96 in each group, is needed.

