## Data collection, management, and analysis

### Data collection methods

All data will be collected prospectively into an electronic database.

The reasons for withdrawal will be carefully documented. The investigator will attempt to contact the subject at least three times prior to designating them as lost to follow-up. The investigator will document the date and type of attempted communication. If a subject cannot be reached during the visit window, a missed visit will be recorded. After three consecutive missed visits, the subject will be considered lost to follow-up, and a study exit form will be completed in the CRFs. Any data on subject participation and procedures until their withdrawal will be analyzed within the research.

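### Deleting patients with missing data turns the planned intention-to-treat comparison into a complete-case comparison, with most exposure on the posted 90-day GIQLI

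*Protocol article*

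**What the plan says.** Statistical methods in the protocol article promises two analysis sets, "Both intention-to-treat and per-protocol analyses will be performed", and closes with one rule for missing data: "If data for a certain variable is missing the case will be removed from the analysis in question". The rule has no exception for the primary endpoint. No assumption about the missingness and no sensitivity analysis accompanies it.

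Four other places bear on it:

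- **Outcomes.** The primary endpoint is 30-day morbidity, "which will be evaluated from the Comprehensive Complication Index (CCI) of all patients".
- **Sample size.** Loss inside the primary window is foreseen: "Assuming a 10% patient drop-out rate during the 30-day follow-up period".
- **Eligibility criteria and Outcomes.** The GIQLI is posted to patients 90 days after surgery.
- **Data collection methods.** For patients who leave, "Any data on subject participation and procedures until their withdrawal will be analyzed within the research".

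**The concern.** This is a chosen method and not a detail left for later. An analysis plan that imputed would contradict the published protocol, and one that followed it would delete.

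An intention-to-treat comparison owes its validity to keeping everyone who was randomised. Once patients with missing values are removed, the groups compared are those who stayed or replied. They remain comparable only if missingness is unrelated to outcome, or under other conditions that the protocol neither states nor examines. Related loss is plausible here. The Blinding section says the technique cannot be concealed after surgery, the Objectives expect faster recovery in one arm, and returning a posted form may depend on how well the patient has recovered. The protocol records age, ASA class, Charlson index, indication and preoperative ICU need, and centre is known from randomisation. Deletion uses none of these to recover information on the missing patients.

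At stake are the size of the treatment difference and, if loss differs by arm, the type I error. The allowance for drop-out protects power only.

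**Working it through.** **Inputs.** Sample size gives the planning rates ("report 48.3% 30-day postoperative morbidity after open surgery and 27.8% after laparoscopy"), 80% power, 87 per group, and 96 per group after 10% drop-out. Statistical methods gives two-sided testing at 0.05 ("Two-tailed *p* values will be reported"; p values "≤ 0.05 are considered significant"). All loss and response patterns below are assumptions, because the protocol gives none.

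**1. The plan's own figure.** Two proportions, pooled variance under the null, no continuity correction:

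n = [1.96 × √(2 × 0.3805 × 0.6195) + 0.842 × √(0.483 × 0.517 + 0.278 × 0.722)]² / 0.205² = 86.9, so 87 per group, as stated. Inflation: 87 × 1.10 = 95.7, so 96. Losing 10% of 96 leaves about 86 per arm and 79.6% power. Power is therefore kept, and the question is bias.

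**2. Same loss mechanism in both arms.** Assume 20% of patients with an event are lost and 4% of those without.

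- Open: 0.483 × 0.80 = 0.386; 0.517 × 0.96 = 0.496; complete-case rate 0.386 / 0.883 = 43.8% (11.7% lost).
- Laparoscopic: 0.278 × 0.80 = 0.222; 0.722 × 0.96 = 0.693; complete-case rate 0.222 / 0.916 = 24.3% (8.4% lost).
- Difference 19.5 points against a true 20.5: a bias of about 1 point. With equal true rates the two arms shift equally, and the bias is zero.

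**3. Loss that differs by arm, no true effect.** Assume 38% in both arms, 10% lost in each, and events in 20% of the lost open patients and 60% of the lost laparoscopic patients.

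- Open: (0.38 − 0.10 × 0.20) / 0.90 = 40.0%. Laparoscopic: (0.38 − 0.10 × 0.60) / 0.90 = 35.6%. Spurious difference 4.4 points.
- With 86 per arm the standard error is √(2 × 0.38 × 0.62 / 86) = 7.4 points, and the two-sided type I error is about 9% instead of 5%.

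**4. Extreme-case bounds.** Let m of 96 be missing in each arm, with 20.5 points observed. The difference in all randomised patients lies within (1 − m/96) × 20.5 ± 100 × m/96.

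| m | lower | upper |
|---|---|---|
| 9 | 9.2 | 28.0 |
| 10 | 7.9 | 28.8 |

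Each end needs every missing patient in one arm to have had an event and none in the other.

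**5. GIQLI, one mechanism in both arms.** Assume a true difference of 0.40 SD and a log-odds of non-response that rises by 0.5 or 1.0 per SD of worse score. With roughly 20% missing, the complete-case difference is 0.385 or 0.355 SD; with roughly 40% missing, 0.377 or 0.341 SD. That is attenuation of up to about 0.06 SD.

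**6. Withdrawal rule beside deletion rule.** Data collection methods keeps what was recorded before withdrawal. Statistical methods drops a patient only from an analysis whose variable is missing. Both can hold together. What neither settles is whether the CCI of a patient who leaves before day 30, built from the complications recorded so far, counts as observed or as missing.

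**The case against.** The best defence is that the primary endpoint is little exposed. The SPIRIT table schedules complications at the procedure, during the stay, at discharge and at 30 days; study personnel complete the forms; and patients make no extra visits. The 10% is a planning allowance and not evidence that outcomes will go unobserved. Imputation models are also commonly left to an analysis plan. The first part stands, and is why the exposure lies mainly with the GIQLI. The last does not answer the point, because the article fixes deletion as the rule.

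Three stronger readings are tempting, and the documents do not support them.

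- **A contradiction with Data collection methods.** A reader might infer one. Step 6 shows that the passages are compatible; only the incomplete CCI is unresolved.
- **The 8-to-29-point range as the likely bias.** Any trial with about 10% missing has such bounds, imputation would not narrow them, and they sit on the binary planning scale while the endpoint is the CCI.
- **A large spurious GIQLI effect.** With no true difference and assumed response of 65% against 85%, slopes of 0.5 and 1.0 give 0.093 and 0.160 SD. But if recovery is equal, response that depends on recovery cannot create a 20-point gap. A separate effect of arm on response is needed, and no passage suggests one. In that scenario the bias also runs against the better-responding arm, because the 65% arm's mean is inflated more (0.16 to 0.29 SD against 0.07 to 0.13 SD).

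A fair criticism of any remedy also stands: imputation that assumes data missing at random does not cure loss that depends on the unobserved score. In the same scenario, with predictors correlated 0.3 to 0.5 with the GIQLI (assumed), it leaves about 0.07 to 0.09 of the 0.093 SD and 0.12 to 0.15 of the 0.160 SD.

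**Conclusion.** The point holds. A stated deletion rule undercuts the promised intention-to-treat analysis and a primary endpoint described as covering all patients.

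The bias is conditional. If loss is unrelated to outcome there is none. If loss is related to outcome in the same way in both arms, it is about 1 point on the primary planning scale and zero under the null. If loss differs by arm it can be larger: 4.4 points and a type I error near 9% in the assumed example, with bounds of about 8 to 29 points as the outer limit. Nothing in the protocol shows which case applies. The GIQLI is the more exposed outcome because it depends on a returned form, and no response rate is given. The rule should be changed, but it does not by itself invalidate the primary result.

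**What to change.** Replace the deletion sentence in Statistical methods by amendment, before comparative data are examined:

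1. Define intention-to-treat as all randomised patients, analysed by allocated arm.
2. For the CCI, use complications recorded up to exit together with available hospital records to day 30, and say how a CCI that is still incomplete is treated.
3. Impute remaining missing CCI, and GIQLI in survivors, by multiple imputation within arm, using centre, indication, age, ASA class, Charlson index and preoperative ICU need, plus the 30-day CCI for the GIQLI.
4. State how deaths before day 90 enter the GIQLI analysis, since imputation covers survivors only.
5. Add a delta-adjusted or tipping-point sensitivity analysis for data missing not at random. Item 3 alone does not address that case.
6. Report complete-case results as supportive only.

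The cost is amended wording, some extra analysis in standard software and a missing-at-random assumption that must be stated. The baseline predictors are already collected, so no new data item or patient contact is needed.
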